## 4. STUDY DESIGN

A two-arm parallel RCT with a wait-list controlled design in which the control group may pursue professional development activities as usual and will receive access to the intervention following the final study assessment nine-months post-randomization. Assessors will be blind to group assignment. Target sample sizes were determined based on power analyses. The unit of randomization is the individual participant. The co-primary outcomes are psychological distress and well-being. Participants will complete assessments at baseline, prior to random assignment, after weeks one, three, five, eight and twelve (i.e., post-intervention), and after weeks 24 and 36. A subset of 510 participants (255 from each condition) will be selected for a dried blood spot substudy in which dried blood samples will be collected at baseline, week 12 and week 24. A subset of 510 participants, ideally overlapping with the dried bloodspot substudy, will be selected for the patient satisfaction substudy in which enumerators assess participants' patients perspectives on their care.

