### 8.2 SAMPLE SIZE AND POWER ANALYSES

Our target sample size was informed in part by our agreements with State Ministers of Health, which requested a minimum number of participants from each participating state. Because of the large, planned sample size (up to 4,000), we conducted two power analyses. First, we conducted a sensitivity power analysis to determine the smallest detectable effect based on the lower bound of the expected intention-to-treat sample of 4,000. To ensure our power estimates were conservative, we based power calculations off of the Bonferroni corrected two-tailed p-value assuming that all primary and secondary outcomes in the parent trial share the same family-wise error 0.05 error rate. We plan to test a total of 9 primary and secondary outcomes for a Bonferroni corrected error rate of 0.006. For measures collected at all 10 assessments points, we assume:

- 0.80 power
- A correlation of  $r = .50$  between the same measure at different assessments
- Error rate of 0.006

Under the above conditions, we will be able to detect a significant group by time interaction effect of Cohen's  $d \geq 0.04$ . For measures assessed at five of the timepoints, assuming the same conditions listed above, we will be able to detect between group effects of Cohen's  $d \geq 0.05$ .

We conducted a second power analysis to determine the size of the randomly selected biomarker and patient satisfaction report subsample required to detect a pre- to post-test change of  $d \geq 0.15$ . We selected  $d \geq 0.15$  as our expected effect size because, in two meta-analyses on the topic of mindfulness-based interventions effects on inflammation,  $d \geq 0.15$  was the smallest observed average effect size on the cytokines we will assay. We assume:

- 0.90 power
- A correlation of  $r = .60$  between the same measure at different assessments
- Error rate of 0.005

In order to detect a statistically significant group by time interaction effect of Cohen's  $d \geq 0.15$  on our measures of peripheral inflammation, we will require a subsample of 468 participants. Assuming 10% of selected participants do not provide a pre-test sample, we plan to randomly select 255 participants from each group (510 total) to participate in biomarker data collection.

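### The second power analysis in section 8.2 does not give 90% power for the pre- to post-test change it names, and it has no stated basis for patient satisfaction

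*Protocol*

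**What the plan says.** Protocol section 8.2 describes a second power analysis, done "to determine the size of the randomly selected biomarker and patient satisfaction report subsample required to detect a pre- to post-test change" of d = 0.15 or more. The inputs are 0.90 power, r = .60 "between the same measure at different assessments", and "Error rate of 0.005". The effect size is explained by literature on inflammation: 0.15 "was the smallest observed average effect size on the cytokines we will assay". The result, 468 participants, is stated for a group-by-time interaction on peripheral inflammation. With an allowance of 10% for missing pre-test samples, 255 per arm (510 in total) are to be selected for biomarker collection.

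Section 4 gives the blood-spot substudy three collections: baseline, week 12 and week 24. It then says that another 510 participants, ideally overlapping with the first, "will be selected for the patient satisfaction substudy in which enumerators assess participants' patients perspectives on their care". Neither section states how many times patients are assessed, how many patients there are per provider, or whether the same patients are seen again.

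**The concern.** Two things do not fit together.

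- The opening sentence of the analysis names a pre- to post-test change, a comparison of two assessments. The sample size appears to come from a test over three. The 90% then belongs to a different test from the one named.
- The opening sentence covers patient satisfaction as well, but the effect size comes only from cytokines. The correlation is carried over without comment to an outcome reported by a different set of people.

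At stake is how a null result is read. If a pre- to post-test comparison is not significant, a reader of section 8.2 would take it that an effect of 0.15 had a 10% chance of being missed. Under the plan's own inputs that chance is about 21% at 468. For patient satisfaction the document supports no figure.

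**Working it through.** **Inputs from section 8.2:** d = 0.15, r = .60, alpha = 0.005, target power 0.90, N = 468 (510 selected), equal arms. The F test is non-directional, which agrees with the two-tailed level used in the first power analysis of that section. From section 4: three blood-spot collections.

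**Formula.** Repeated-measures group-by-time interaction with two groups and m assessments, sphericity assumed:

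- f = d/2 = 0.075, so f² = 0.005625
- noncentrality = N × f² × m / (1 − r)
- df1 = m − 1, df2 = (N − 2)(m − 1)
- power = probability that a noncentral F exceeds the central F critical value at 0.005

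**Step 1: reproduce 468.** With m = 3 and N = 468, noncentrality = 468 × 0.005625 × 3 / 0.40 = 19.74. With df 2 and 932, power is 90.5%. The smallest even N reaching 90% is 464, within 1% of the stated 468. The alternatives at the same alpha and power do not fit:

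| Variant | N for 90% |
|---|---|
| f = 0.075, m = 3 | 464 |
| f = 0.075, m = 2 | 600 |
| f = 0.075, m = 4 | 382 |
| f = 0.15, m = 2 | 154 |
| f = 0.15, m = 3 | 118 |
| Change score, d in raw SD units | 2378 |
| ANCOVA, d in raw SD units | 1902 |

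So the stated figure is most plausibly a three-assessment test with f = d/2, matching the blood-spot schedule.

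**Step 2: the contrast named in the text.** Change only m, from 3 to 2:

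- N = 468: noncentrality = 468 × 0.005625 × 2 / 0.40 = 13.16, df 1 and 466, power 79%
- N = 510: noncentrality = 510 × 0.005625 × 2 / 0.40 = 14.34, df 1 and 508, power 83%
- 90% power needs N = 600

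The 83% supposes that all 510 contribute data. Nothing in this step is specific to one outcome, so it holds for the biomarkers as well as for patient reports.

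**Step 3: patient reports.** Which inputs have a source for this outcome?

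- d = 0.15: the stated source is cytokine results only
- r = .60: no source, and for patients it depends on whether the same people are re-interviewed and on how many are averaged per provider
- number of assessments: not stated

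To show how much r matters, hold f at 0.075 with two assessments and N = 468, and assume other values (none is in the document): r = .50 gives 66%, while r of about .69 gives 90%. The result can move either way.

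**The case against.** The strongest defence is that the numerical claim is already limited to biomarkers. The sentence giving 468 refers to peripheral inflammation and the 510 are selected for biomarker collection, so only the lead-in mentions patient reports. It also calls the test a group-by-time interaction, which fits three assessments. This stands in part: the slip is in how the analysis is introduced. But the lead-in says what the calculation is for, and it names both substudies and a pre- to post-test change. Section 4 then gives the patient-satisfaction substudy the same 510. A reader has no other source for that number.

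It is also fair to say that the two-assessment shortfall is not peculiar to patient reports. That is accepted, and the point covers both outcomes.

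A reader might go further and infer that the patient-satisfaction substudy is badly underpowered, because different patients at each assessment would pull the correlation well below .60. The document does not support that. It does not say that patients differ between assessments, how many are seen per provider, or how often. Nor does it fix the unit of d. As an illustration under assumed values (intraclass correlation 0.10 within provider, five different patients at each of two assessments, N = 468), power is about 52% if 0.15 is in SDs of the provider mean, and about 99.5% if it is in SDs of individual patients. Even the direction is open.

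Lastly, patient satisfaction is not among the outcomes listed in section 6.1, so the consequence is limited.

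**Conclusion.** The point holds in a limited form. Section 8.2 attaches 90% power to a pre- to post-test change, while its sample size delivers that only for a three-assessment interaction. For two assessments the plan's own inputs give about 79% at 468 and 83% at 510, for biomarkers and patient reports alike. Separately, the document gives no basis for d = 0.15 or r = .60 in patient reports, so no power figure can be claimed for them, high or low.

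This rests on two inferences: that the calculation used three assessments, and that it used f = d/2. Neither is stated; both follow from the fact that this combination comes close to 468 and the other variants tried do not. The 79% and 83% also take d = 0.15 and r = .60 as given.

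**What to change.** In section 8.2:

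1. Remove the mention of patient satisfaction reports from the purpose of the second power analysis. State that the size of that substudy follows from its overlap with the blood-spot subsample, and that no 90% power is claimed for it.
2. Say that 468 and 90% refer to the group-by-time test over the three blood-spot assessments, for the biomarkers.
3. Add that the two-assessment, pre- to post-test power under the same inputs is about 79% at 468 and 83% at 510.
4. If a figure for patient satisfaction is wanted, derive it from that substudy's own number of assessments, with patients nested within provider and the unit of d stated, and show it over a range of correlations.

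The cost is protocol wording and a short recalculation. No further participants are needed. The stated power for the pre- to post-test contrast becomes less favourable.

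### The biomarker subsample of 468 does not give 90% power for a between-arm pre-to-post difference of d = 0.15; on that reading power is about 16–22%

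*Protocol*

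**What the plan says.** Section 8.2 contains a second power analysis, for the biomarker and patient satisfaction subsample. Its aim is to size the "subsample required to detect a pre- to post-test change of" d at least 0.15. The section calls 0.15 the expected effect size and explains that, in two meta-analyses, it "was the smallest observed average effect size on the cytokines we will assay". The inputs are 0.90 power, r = .60 between assessments and "Error rate of 0.005". The first power analysis in the same section uses a "Bonferroni corrected two-tailed p-value"; the second does not state sidedness.

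The conclusion is that, to detect a group-by-time interaction of d at least 0.15, "we will require a subsample of 468 participants". Allowing for 10% without a pre-test sample, "we plan to randomly select 255 participants from each group (510 total").

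Section 4 says that "dried blood samples will be collected at baseline, week 12 and week 24". Section 8.2 does not name the test, say how many visits entered the calculation, or say in what SD units d is expressed and how it was converted for an interaction test.

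**The concern.** A difference of 0.15 SD is small, and 0.005 is a strict error rate. With 234 per arm the standard error of a between-arm difference in change is about 0.08 SD. An effect of 0.15 is then less than two standard errors, while 90% power at this alpha needs about four. The stated power cannot be right if d means what the text suggests, namely a treatment effect on pre-to-post change.

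Peripheral inflammation is named in the study objectives (section 2), and CRP, IL-6, IL-10 and TNF-alpha are listed among the secondary outcomes (section 6.1.2). A reader who trusts the 90% figure would take a non-significant biomarker result as strong evidence against an effect of 0.15. On the plan's assumptions, the chance of detecting that effect in the pre-to-post comparison at 0.005 was about one in five or less.

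**Working it through.** **Inputs (section 8.2 unless noted).** d = 0.15; r = .60; power 0.90; alpha 0.005, taken as two-sided; N = 468, so 234 per arm; three blood samples (section 4). Normal quantiles: 2.807 for two-sided 0.005, 1.960 for two-sided 0.05, 1.282 for 90% power.

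**1. Where 468 may come from.** Repeated-measures interaction F test, two groups, m visits, noncentrality f² × N × m / (1 − r).
- f = d/2 = 0.075, m = 3: 90% power needs N = 464. At N = 468 the noncentrality is 0.005625 × 468 × 3 / 0.4 = 19.7 and power is 90.5%.
- f = 0.075, m = 2 (the pre-to-post contrast): N = 600, and power at 468 is 79%.

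The three-visit version is close to 468 but not exact.

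**2. What that f means.** In a 2 × 2 (two-arm, two-visit) interaction, a between-arm difference in change of d SD corresponds to f = d/4. So f = 0.075 stands for 0.30 SD, and 0.15 SD is f = 0.0375. With f = 0.0375 and m = 2, power at 468 is 15.8%, and 90% power needs N = 2,382.

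**3. Direct calculation for a between-arm difference of 0.15 SD.** Power = Φ(0.15/SE − z).
- Change score: SE = √(2 × 2(1 − .60)/234) = √(2 × 0.80/234) = 0.0827. 0.15/0.0827 = 1.81; 1.81 − 2.807 = −0.99; power 16.0%.
- Baseline-adjusted: SE = √(2 × (1 − .60²)/234) = √(2 × 0.64/234) = 0.0740. 0.15/0.0740 = 2.03; 2.03 − 2.807 = −0.78; power 21.8%.
- N for 90% power, 4 × (2.807 + 1.282)² × variance factor / 0.15²: about 2,378 (factor 0.80) or 1,902 (factor 0.64).
- Effect detectable with 90% power at 468, (2.807 + 1.282) × SE: 0.34 or 0.30.

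**4. More favourable readings at N = 468.**

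| Reading | Two-sided 0.005 | Unadjusted two-sided 0.05 |
|---|---|---|
| Change score, pre to post | 16% | 44% |
| Baseline-adjusted, pre to post | 22% | 53% |
| Baseline-adjusted mean of weeks 12 and 24, effect sustained | 36% | 69% |

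The last row uses the variance factor (1 + .60)/2 − .60² = 0.44. A one-sided 0.005 test gives 22% (change score) or 29% (baseline-adjusted) for the pre-to-post contrast. Reading d as an uncontrolled change within one group needs (2.807 + 1.282)² × 0.80 / 0.15² ≈ 594 people in that group, so even all 468 pooled would fall short.

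**5. The allowance for loss.** 510 × 0.9 = 459, not 468; keeping 468 would need 468/0.9 = 520. With 459, SE = √(4 × 0.80/459) = 0.0835 or √(4 × 0.64/459) = 0.0747. Power for 0.15 is 15.6% or 21.2%, and the effect detectable with 90% power is 0.34 or 0.31.

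**6. What a non-significant result could show (N = 468).** The 95% confidence interval half-width is 1.96 × SE = 0.162 (change score) or 0.145 (baseline-adjusted). The upper limit stays below 0.30 if the estimate is below about 0.14 or 0.155. But an estimate can be as large as 2.807 × SE = 0.23 or 0.21 and still miss significance at 0.005, and its upper limit would then be above 0.30.

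**The case against.** The strongest reply is that the protocol does not say how 468 was obtained. It names no test, software, number of visits, conversion or SD unit, and section 8.4 points to a preregistration that is not to hand. A reader might infer that the authors demonstrably used f = d/2. The documents do not show this: the reconstruction gives 464 and remains an inference. The 0.30 SD equivalence also belongs to the two-visit test, not the three-visit one. This part of the objection stands. It does not rescue the claim, because the direct calculation in step 3 does not depend on how 468 arose.

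Second, section 8.4 does not test at 0.005. It applies a false discovery rate correction at two-tailed 0.05 in a mixed model, and week 24 adds information. This also stands: 16–22% is the power of the pre-to-post contrast at the sizing alpha, not necessarily that of the final analysis. The unadjusted 0.05 column, which is more lenient than any corrected rule, still stops at 53% for that contrast and 69% for the averaged follow-up.

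Third, a reader might conclude that a null biomarker result would be uninformative. That goes too far. With a half-width of 0.145 to 0.162 SD, a result near zero would exclude effects of about 0.30. It is effects near 0.15 that the substudy is poorly placed to detect.

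Fourth, the biomarkers are secondary outcomes in a substudy, and the co-primary outcomes do not depend on 468. That limits the reach of the error but does not correct the printed claim.

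**Conclusion.** The concern holds in limited form. The statement that 468 participants give 90% power for d = 0.15 is not supported by the section's own inputs when d is the between-arm difference in pre-to-post change in raw SD units. Power is about 16% (change score) or 22% (baseline-adjusted) at two-sided 0.005, and at most 44–53% at unadjusted 0.05. No reading examined that takes 0.15 as that difference comes near 90%. At 0.005 the subsample has 90% power for about 0.30 to 0.34 SD, roughly twice the stated effect.

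The conclusion rests on r = .60, equal variances, two-sided testing and that definition of d. The f = d/2 explanation is probable but not established. Nor does the text call 0.15 the smallest plausible effect, as a reader might infer: it is the expected effect size, chosen as the smallest average effect in two meta-analyses.

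**What to change.** Keep the subsample and remove the claim that 468 detects d = 0.15 with 90% power. Replace it with wording such as:

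> With 459 analysable participants (510 less 10%), r = .60 and two-sided alpha 0.005, the substudy has 90% power for a between-arm difference in pre-to-post change of about 0.31 SD (baseline-adjusted) to 0.34 SD (change score). Power for 0.15 SD is about 16% (change score) to 21% (baseline-adjusted).

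If 468 is kept as the reference number, the corresponding figures are 0.30 to 0.34 SD and 16–22%.

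State also the test behind the calculation, the number of visits used, the SD unit of d and any conversion to f. Report biomarker effects as estimates with confidence intervals. Say that a non-significant result does not by itself exclude d = 0.15, although the interval may exclude effects of about 0.30 or more.

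The change costs wording only. Recruitment closed in May 2023 and version 1.1 is dated December 2024, so this is a correction to the stated power and to how results are read, not a call for more participants or a new prior declaration. The downside is that the stated detectable effect becomes less favourable.

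### The biomarker substudy's 510 selected participants fall 9 short of the required 468 after the plan's own 10% loss, and selecting by group conflicts with a baseline sample taken before assignment

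*Protocol*

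**What the plan says.** Section 8.2 of the Protocol contains a second power analysis for the biomarker subsample. It targets a pre- to post-test effect of d = 0.15 with 90% power, an error rate of 0.005 and a correlation of 0.60 between assessments, and concludes that "we will require a subsample of 468 participants". The next sentence sets the allowance for loss and the number to be drawn: "Assuming 10% of selected participants do not provide a pre-test sample, we plan to randomly select 255 participants from each group (510 total".

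Section 4 repeats the number and the selection by arm: "A subset of 510 participants (255 from each condition) will be selected for a dried blood spot substudy". It places the blood samples at baseline, week 12 and week 24. On the order of events the same section says: "Participants will complete assessments at baseline, prior to random assignment". The schedule in section 7.2 marks dried blood spots in the Baseline column. Section 6.1.2 lists the biomarkers (CRP, IL-6, IL-10, TNF-alpha) among the secondary outcomes.

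**The concern.** There are three linked difficulties.

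- **The inflation does not reach the stated requirement.** The 10% is defined as a share of those selected, so the number left can be worked out directly, and it is below 468.
- **The allowance covers one sample only.** A change from baseline to week 12 needs both samples. The only loss allowed for is at baseline.
- **The order of steps is contradictory.** Groups exist only after assignment. A draw from each group, with some of those drawn then failing to give a baseline sample, puts selection after assignment and the spot after selection. Sections 4 and 7.2 put baseline first.

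The third matters most for interpretation. The comparator is a wait list, and only assessors are described as blind. If participants knew their arm when asked for the first spot, willingness to give it could differ between arms, and the biomarker groups would no longer be comparable by randomization alone.

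**Working it through.** **Inputs (section 8.2 unless noted).** Required N = 468; selected N = 510 (255 per group); loss = 10% of those selected; d = 0.15; power 0.90; error rate 0.005; r = 0.60. Three blood samples (section 4). Assumed here: the conversion f = d/2 = 0.075.

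**Step 1. Reproduce 468.** For a two-group repeated-measures interaction with m measurements, the noncentrality is λ = f² × N × m / (1 − r), with degrees of freedom (m − 1) and (N − 2)(m − 1). With m = 3, the smallest even N reaching 90% power is 464, within 1% of 468. At N = 468, λ = 0.075² × 468 × 3 / 0.40 = 19.74 and power is 90.5%. This is the closest match found with the stated inputs. With m = 2 the same method needs 600.

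**Step 2. Check the inflation.**
- Left after 10% loss: 510 × 0.90 = 459; 468 − 459 = 9 short (1.9%).
- Loss that 510 can absorb: 1 − 468/510 = 8.2%.
- Number needed for 10% loss: 468 / 0.90 = 520, or 260 per group.
- The common shortcut, 468 × 1.10, gives 515, so it does not explain 510 either.

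**Step 3. What the shortfall costs (method of step 1, m = 3).**

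| N with data | Power |
|---|---|
| 468 | 90.5% |
| 459 | 89.7% |
| 510 (no loss) | 93.3% |

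The shortfall costs about 0.7 points against 468 and 0.3 points against the 90% target.

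**Step 4. Loss after baseline.** The documents give no rate. As an assumption, take a further 10% to 20% without a week-12 sample:
- 459 × 0.90 = 413, power about 85.1%;
- 459 × 0.80 = 367, power about 79.0%.

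These figures count only participants with complete data.

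**Step 5. Order of steps, side by side.**

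| Place | What it implies |
|---|---|
| Section 8.2 | Selection is by group, and some of those selected then give no baseline sample: assignment, then selection, then spot |
| Section 4, substudy sentence | Equal numbers per condition: assignment, then selection |
| Section 4, assessment sentence | Baseline assessments, then assignment |
| Section 7.2 | Dried blood spots belong to Baseline |

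The first two rows cannot both hold with the last two unless the blood spot is an exception to the baseline rule or the draw does not use allocation. The Protocol states neither.

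**The case against.** The strongest reply is that the slip does not matter. Nine people are 1.9% of the sample, and power stays within 0.3 points of target. At the 0.006 error rate used for the parent trial, the same method needs only 452, which 459 would meet. All of this stands: a reader might infer that the substudy is materially underpowered, and the documents do not support that.

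On later loss, the 10% to 20% is not a figure from the plan. Section 8.4 specifies linear mixed models with maximum likelihood, which keep participants with partial records, and a third sample at week 24 adds information. The 413 and 367 are therefore not the plan's analysable numbers, and the true loss of power would be smaller than the complete-data figures show. What remains is that a participant without a week-12 sample carries less information on the target contrast, and the plan makes no allowance for this.

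On sequence, a reader might infer that the baseline spot was taken after participants learned their arm. No section says so. Assignment by REDCap (section 7.1) is not the same as disclosure, and the Protocol does not say when participants are told. Differential refusal would need both assignment and disclosure to precede the spot. Section 8.4 also plans pattern-mixture modelling if attrition differs between groups, a partial safeguard. The contradiction over timing nevertheless stands, because nothing in the document resolves it.

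**Conclusion.** The concern holds in a limited form. The stated selection number is wrong by the Protocol's own assumption: 459 expected with a baseline sample against 468 required. This needs no outside input. It is an internal inconsistency with a negligible power cost (89.7% against 90.5%).

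The power figures rest on the three-measurement calculation with f = d/2, which approximates 468 but does not return it exactly. An exact 468 appears with three measurements, r = 0.50 and power 0.80, which are not the inputs stated for this analysis, so the inputs actually used should be confirmed.

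The missing allowance for week-12 loss is a real gap of unknown size. The range of about 85% to 79% is illustrative and overstates the loss under the planned model.

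The order of selection, baseline spot and assignment is contradictory as written. Bias from known allocation is a possibility that the text leaves open, not something it establishes. The point concerns a secondary-outcome substudy and does not touch the co-primary analyses.

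**What to change.** 1. In section 8.2, give 459 as the expected number with a baseline sample, or change the selected number to 520 (260 per group) if selection is still open, and carry the change into section 4. The recruitment window was to close on May 21, 2023 and version 1.1 is dated 12.20.2024, so restating the expected number is probably the only practicable choice.
2. State how many are expected to have both baseline and week-12 samples, and give the power or detectable effect for that number. Name the method and the number of measurements used.
3. Reconcile sections 4, 7.2 and 8.2 by stating when the subsample was drawn and when the baseline spot was taken, relative both to assignment and to its disclosure to participants.
4. If the spot followed disclosure, report by arm the numbers selected and the numbers giving a baseline sample, and treat possible differential provision as a limitation of the biomarker comparison.

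The cost is a few sentences and one recalculation. If selection is still open and 520 is chosen, there is also the collection and assay of samples from up to 10 more participants. No change to the main trial is needed.
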